### Sample Size

Considering that the focus of this pilot study is to have patients with bipolar disorder in different mood states (depression, euthymia, and hypomania), a conservative approach for calculating the sample size was adopted (ie, concordant pairs) to ensure more qualitative feedback [52]. The overall mood/behavior states assessed using the *Toi Même* app encompasses 8 dimensions of behavior (ie, mood, energy, emotion, irritability, anxiety, activity, speech, and thought speed). Each of these dimensions is rated using a score ranging from –3 to +3, yielding a total score of 24. Accordingly, a concordant pair between the app measurements and the clinical assessments of mood symptoms was defined as follows: (1) depression, a score of <–8 in the app assessments and scores of >15 for MADRS and <8 for YMRS; (2) euthymia, a score between –8 and +8 in the app assessments and scores of <15 for MADRS and <8 for YMRS; (3) (hypo)mania, a score of >+8 in the app and scores of <15 for MADRS and >8 for YMRS. Assuming that the expected proportion of the concordant pairs is 98%, with an estimated precision of 5% and a two-sided 95% CI, 31 patients will be included in each of the 3 groups to fully accomplish the study goals (N=93).

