### Outcome Measures

Outcome measures are assessed at the baseline visit and after 2 weeks, 1 month, 2 months, and 3 months [50]. Briefly, primary outcome measures focus on changes in the severity of the depressive and manic symptoms assessed using the MADRS and YMRS. Secondary outcomes include changes in the self-rated mood/behavioral symptoms and medication adherence assessed using the self-report instruments QIDS-SR, Altman Self-Rating Mania, Multidimensional Assessment of Thymic States, and the Medication Adherence Rating Scale [51]. Functioning will be assessed using the FAST scale. Feasibility measures include the proportion of eligible participants who have consented to participate in the study, the frequency of self-assessments, and the proportion of participants who continued using *Toi Même* app during the study period. The participant’s physical activity will be inferred using the number of steps and distance automatically captured by the smartphone motion sensors.

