### Statistical Analysis

Descriptive analyses will be conducted to characterize the sociodemographic and clinical characteristics of the initial sample as well as the retention at the end of the study. Receiver operating characteristics analysis will be applied to calculate the concordance ratio of the pairs (ie, the area under the curve) [53]. Given that patients have started using the app from the baseline visit, the clinical data collected at this time point will not be included in the concordant pairs’ analysis. Compliance will be calculated as the proportion of the enrolled patients completing the first 15 and then 30 and 90 consecutive days of ratings. The app completion rate would be completing at least 70% of the momentary assessments during the time a participant has continued in the study. The average ratings of the perceived helpfulness, ease of use, and overall satisfaction would be at least 3 on the 1 to 5 rating scores. Cluster analysis will be performed using principal component analysis (PCA) to identify groupings of the daily *Toi Même* mood/behavior questions. The PCA results will be then used to obtain a single summary statistic (*TM*P1) that will account for the maximum amount of variability in the 8 daily *Toi Même* mood/behavior responses across all the subjects during the study period. The summary statistic produced from the PCA-*TM*P1 will be used as a response to test for differences between groups in daily ratings and for comparison between this app score and the clinical rating scores. To test for differences between groups over time, linear mixed regression models will be used with autoregressive covariance adjustments for repeated measurements of continuous outcomes and logistic generalized estimating equations will be used for binary outcomes. In both linear and logistic generalized estimating equation models, adjustments for sex, age, day of the week, and elapsed time in the study will be included as other covariates in the models. The regularity in the daily ratings for each subject will be estimated using the root mean squared successive differences (a measure of the variability of the changes in scores over time), the Teager-Kaiser Energy Operator, which combines amplitude and frequency, and the information entropy, which measures regularity of amplitude [37]. The within-subject sample variance will be also used as a measure of regularity for each subject’s response and will estimate the distribution of the amplitudes recorded over time. Data analysis will employ the intention-to-treat principle by including all participants in the analyses, which will be conducted using the R programming language (R Core Team).

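### The 31 per group follows from the stated inputs, but by a normal approximation that fails near 100%, so the 5% precision is not reliably delivered

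*Protocol article*

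**What the plan says.** The Sample Size section of the protocol article defines a concordant pair by joint cut-offs on the app score, MADRS and YMRS, separately for depression, euthymia and (hypo)mania. The size is then set by precision: "Assuming that the expected proportion of the concordant pairs is 98%, with an estimated precision of 5% and a two-sided 95% CI". From this it concludes: "31 patients will be included in each of the 3 groups to fully accomplish the study goals (N=93". The section introduces the method with the words "a conservative approach for calculating the sample size was adopted (ie, concordant pairs". It gives no basis for the 98% and does not name the interval method.

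Two other sections bear on the number of pairs. Under Outcome Measures, "Outcome measures are assessed at the baseline visit and after 2 weeks, 1 month, 2 months, and 3 months". Under Statistical Analysis, baseline is set aside: "the clinical data collected at this time point will not be included in the concordant pairs’ analysis". That leaves up to four follow-up visits per patient at which a pair could be formed. The Sample Size section counts patients only.

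**The concern.** A proportion expected at 98% in 31 patients leaves well under one expected discordant patient. The normal approximation is unreliable that close to the boundary, so a half-width of about 5 points computed from it does not describe the interval the trial will obtain.

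The input also pulls the wrong way. The variance p(1−p) shrinks as p approaches 1, so 98% gives nearly the smallest sample size the formula can return. If agreement is lower, precision worsens quickly. A pair must satisfy three cut-offs at once, and no support for 98% is offered.

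At stake is how the agreement in each mood state will be read. A reader who takes the stated 5% at face value will think each group's concordance is known more closely than 31 patients allow.

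**Working it through.** **Inputs (Sample Size section).** Expected concordance p = 0.98; precision d = 0.05, read as half-width; two-sided 95%, z = 1.96; 31 patients per group, three groups. One pair per patient is my assumption for steps 1 to 4, because the section counts patients.

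**1. The plan's own figure.** n = z² p(1−p) / d² = 1.96² × 0.98 × 0.02 / 0.05² = 0.0753 / 0.0025 = 30.1, rounded up to 31. It is reproduced. Two other readings do not fit: a one-sided z gives 21.2 (22), and 5% as the full width gives 120.5 (121).

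**2. How that formula behaves at n = 31 and p = 0.98.**
- Planned half-width: 1.96 × √(0.98 × 0.02 / 31) = 4.93 points. The interval is 93.1% to 102.9%, which passes 100%.
- Expected discordant patients: 31 × 0.02 = 0.62.
- Probability that all 31 agree: 0.98³¹ = 53.5%. The Wald interval then has zero width and misses 98%.
- Summing the binomial probabilities of the outcomes whose Wald interval contains 98% gives a true coverage of 46.5%, against a nominal 95%.

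**3. Other intervals at n = 31 (95%, half-width in points).**

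| Concordant | Probability at 98% | Clopper-Pearson CI | Clopper-Pearson | Wilson | Mid-P | Jeffreys |
|---|---|---|---|---|---|---|
| 31/31 | 53.5% | 88.8–100% | 5.6 | 5.5 | 4.6 | 3.9 |
| 30/31 | 33.8% | 83.3–99.9% | 8.3 | 7.8 | 7.4 | 6.9 |
| 29/31 | 10.4% | 78.6–99.2% | 10.3 | 9.5 | 9.3 | 8.9 |

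The upper limit of the Jeffreys and mid-P intervals at 31/31 is set to 100%. Averaged over outcomes at a true 98%, the half-width is 7.2 points (Clopper-Pearson) or 6.8 (Wilson). The average distance from the estimate down to the lower limit is 12.5 or 12.1 points. Even Wald gives 6.2 points at 30/31 and 8.6 at 29/31.

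**4. If concordance is below 98% (assumed range).** Wald half-width at n = 31, its ratio to the planned 4.93, and the n per group the same formula would need for 5 points:

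| Concordance | Half-width | Ratio | n for 5 points |
|---|---|---|---|
| 95% | 7.7 | 1.6 | 73 |
| 90% | 10.6 | 2.1 | 139 |
| 80% | 14.1 | 2.9 | 246 |

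**5. If four follow-up pairs per patient are pooled.** There are 31 × 4 = 124 pairs and 124 × 0.02 = 2.48 expected discordant pairs. With within-patient correlation ρ (not given, so a range), the effective number is 124 / (1 + 3ρ). Clopper-Pearson at 98%:

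| ρ | Effective n | Half-width | Distance to lower limit |
|---|---|---|---|
| 0 | 124 | 3.0 | 4.3 |
| 0.1 | 95.4 | 3.5 | 5.2 |
| 0.4 | 56.4 | 4.9 | 7.9 |
| 0.5 | 49.6 | 5.3 | 8.7 |
| 1 | 31 | 7.4 | 12.7 |

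The half-width stays within 5 points up to ρ of about 0.4. The lower arm does so only below about 0.1.

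**The case against.** The best defence is that nothing was miscalculated. The 31 follows from the inputs, and on the formula's own terms the half-width is 4.93 points, under a stated planning assumption. The arithmetic part of that stands, so this is no arithmetic error. It does not make the approximation suitable.

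Several stronger readings are tempting, and the document does not support them.

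- A reader might infer that no sound interval can be within 5 points at n = 31. Mid-P and Jeffreys are, but only when all 31 agree. Once one patient is discordant, every method in the working misses 5 points.
- A reader might infer that the article calls the 98% conservative. It does not: the adjective describes the choice of the concordant-pairs approach. What can be said is that an approach so described rests on a near-best-case proportion.
- A reader might infer that the results will carry Wald intervals. Statistical Analysis names none. It plans a receiver operating characteristic analysis for concordance, and the interval method may be fixed in an analysis plan that is not shown.
- A reader might infer that any shortfall from 98% makes the estimate two to three times less precise. That needs concordance of about 90% down to 80%; at 95% the factor is 1.6.

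The repeated visits are a fair point. Up to four pairs per patient could bring the half-width within 5 points if the correlation is low. That correlation is unknown, and the Sample Size section does not bring the repeats in.

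Finally, this is described as a pilot, the primary outcomes are changes in MADRS and YMRS, and nothing is decided on the 5%. That lowers the severity. It does not excuse a precision that the article itself states.

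**Conclusion.** The point holds as a fault of method and of the stated precision, with moderate severity. The 31 is correctly computed from a Wald formula that is invalid with 0.62 expected discordant patients per group. With one pair per patient and a true 98%, the expected Clopper-Pearson half-width is 7.2 points against the stated 5. It runs from 5.6 points with no discordant patient to 8.3 with one and 10.3 with two. Clopper-Pearson and Wilson never reach 5 points at n = 31.

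If true concordance is between 95% and 80%, the half-width is about 7.7 to 14.1 points, or 1.6 to 2.9 times the planned 4.9. These figures rest on one pair per patient. Pooling four visits would meet 5 points only with within-patient correlation up to about 0.4 for the half-width, or below about 0.1 for the lower limit.

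**What to change.** Keep N=93 and revise the Sample Size section:

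- Replace the 5% precision with what 31 patients give: exact 95% CIs of 88.8–100% at 31/31, 83.3–99.9% at 30/31 and 78.6–99.2% at 29/31, and about ±7.7, ±10.6 and ±14.1 points at 95%, 90% and 80% concordance.
- State that this assumes one pair per patient. If follow-up visits are to be pooled, give the clustered figure with the assumed within-patient correlation.
- Say that the concordance proportion will be reported with a Wilson or Clopper-Pearson interval, not Wald.
- Remove the statement that 31 per group will meet the study goals in full. If the approach is still described as conservative, say that this does not extend to the 98%.

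The cost is wording only. No patients or visits are added, and the stated precision becomes less favourable.

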### Statistical Analysis

Descriptive analyses will be conducted to characterize the sociodemographic and clinical characteristics of the initial sample as well as the retention at the end of the study. Receiver operating characteristics analysis will be applied to calculate the concordance ratio of the pairs (ie, the area under the curve) [53]. Given that patients have started using the app from the baseline visit, the clinical data collected at this time point will not be included in the concordant pairs’ analysis. Compliance will be calculated as the proportion of the enrolled patients completing the first 15 and then 30 and 90 consecutive days of ratings. The app completion rate would be completing at least 70% of the momentary assessments during the time a participant has continued in the study. The average ratings of the perceived helpfulness, ease of use, and overall satisfaction would be at least 3 on the 1 to 5 rating scores. Cluster analysis will be performed using principal component analysis (PCA) to identify groupings of the daily *Toi Même* mood/behavior questions. The PCA results will be then used to obtain a single summary statistic (*TM*P1) that will account for the maximum amount of variability in the 8 daily *Toi Même* mood/behavior responses across all the subjects during the study period. The summary statistic produced from the PCA-*TM*P1 will be used as a response to test for differences between groups in daily ratings and for comparison between this app score and the clinical rating scores. To test for differences between groups over time, linear mixed regression models will be used with autoregressive covariance adjustments for repeated measurements of continuous outcomes and logistic generalized estimating equations will be used for binary outcomes. In both linear and logistic generalized estimating equation models, adjustments for sex, age, day of the week, and elapsed time in the study will be included as other covariates in the models. The regularity in the daily ratings for each subject will be estimated using the root mean squared successive differences (a measure of the variability of the changes in scores over time), the Teager-Kaiser Energy Operator, which combines amplitude and frequency, and the information entropy, which measures regularity of amplitude [37]. The within-subject sample variance will be also used as a measure of regularity for each subject’s response and will estimate the distribution of the amplitudes recorded over time. Data analysis will employ the intention-to-treat principle by including all participants in the analyses, which will be conducted using the R programming language (R Core Team).

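### The trial is sized on the proportion of app-clinician concordant pairs, but the analysis defines that concordance as an area under the ROC curve, which is a different quantity

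*Protocol article*

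**What the plan says.** The Sample Size section of the protocol article gives one definition of a concordant pair for each mood state. The middle one reads: "euthymia, a score between –8 and +8 in the app assessments and scores of <15 for MADRS and <8 for YMRS". For depression, an app total under −8 must go with MADRS over 15 and YMRS under 8. For (hypo)mania, a total over +8 must go with MADRS under 15 and YMRS over 8.

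The app score is the sum of eight items: "Each of these dimensions is rated using a score ranging from –3 to +3, yielding a total score of 24". It therefore runs from −24 to +24, with euthymia as the middle band. The sample size follows from a proportion: "Assuming that the expected proportion of the concordant pairs is 98%, with an estimated precision of 5% and a two-sided 95% CI". This leads to 31 patients in each of three groups, 93 in all.

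The Statistical Analysis section names the estimator: "Receiver operating characteristics analysis will be applied to calculate the concordance ratio of the pairs (ie, the area under the curve"). The same section leaves baseline data out of the concordant-pairs analysis, so the pairs it means are those of the Sample Size section, taken at the later visits. It does not name the ROC marker or the reference state, and it does not say how three states enter a two-class method.

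**The concern.** The word concordant has two meanings here. In the Sample Size section a pair is one patient's app class and clinical class at the same time, and it is concordant when the two agree. In ROC analysis a pair is one case and one non-case, usually different patients, and it is concordant when the case has the more extreme score. The article joins the two as if they were one quantity.

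Correspondence between app and clinician is a stated aim, and the concordance proportion is the only quantity behind N=93. If an AUC is reported in its place, it cannot be set against the planned 98% ± 5%. It could make agreement look better or worse than it is.

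**Working it through.** **Inputs.** From Sample Size: app cut-offs −8 and +8; expected proportion 0.98; precision 0.05; two-sided 95% CI; 31 per group. From Clinical Assessments: post-baseline visits at 2 weeks and 1, 2 and 3 months, so up to four per patient. The score patterns below are constructed for illustration and are not trial data.

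**1. The plan's own figure.** Precision of a single proportion:

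n = 1.96² × 0.98 × 0.02 / 0.05² = 30.1, rounded up to 31; 3 × 31 = 93.

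At n = 31 the half-width is 1.96 × √(0.98 × 0.02 / 31) = 0.049. The stated figure reproduces as the precision of a proportion. The formula contains no AUC.

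**2. Marker = raw app total.** AUC = P(case scores above non-case) + ½ P(tie), with the direction reversed for depression. Only rank order enters, so the ±8 cut-offs play no part.

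*Compressed scores.* Take 31 patients per state, with depressed totals from −7 to −4, euthymic from −2 to +2 and hypomanic from +4 to +7.

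- Depression versus the rest: AUC 1.0. Hypomania versus the rest: AUC 1.0.
- Concordance: 0/31 in depression, 31/31 in euthymia, 0/31 in hypomania; overall 31/93 = 33%.

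*Full agreement, euthymia versus the rest.* Every euthymic total lies above every depressed total and below every hypomanic one. With a high score counted as positive, AUC = n(depressed) / [n(depressed) + n(hypomanic)].

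| Depressed / euthymic / hypomanic | Concordance | Euthymia AUC |
|---|---|---|
| 31 / 31 / 31 | 100% | 31/62 = 0.50 |
| 50 / 31 / 12 | 100% | 50/62 = 0.806 |
| 12 / 31 / 50 | 100% | 12/62 = 0.194 |
| 40 / 48 / 5 | 100% | 40/45 = 0.889 |

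Agreement is perfect in every row, so the AUC varies only with case mix.

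**3. Marker = binary app class (in the state or not).** AUC = (sensitivity + specificity)/2. The concordance within a clinical state is the sensitivity alone.

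- Sensitivity 0.80, specificity 1.00: AUC 0.90, concordance 0.80.
- Sensitivity 0.98, specificity 0.90: AUC 0.94, concordance 0.98.
- Sensitivity and specificity both 0.98: AUC 0.98, concordance 0.98. The two coincide only when sensitivity equals specificity.

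The first gap, 0.10, is twice the planned precision of 0.05. In the compressed example this marker gives sensitivity 0 and specificity 1 for depression, so AUC is 0.5 where concordance is 0%. Under full agreement it gives 1.0 for every state, euthymia included.

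**The case against.** An author could answer that an AUC is itself a proportion of concordant pairs, namely the c-statistic. That is true, and it would be wrong to say that an AUC is never such a proportion. But its pairs are case/non-case pairs between patients, while the Sample Size section defines agreement within a patient.

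An author could also say that the extreme examples rest on a marker that the article does not specify. This stands too. A reader might infer that the planned analysis must give 0.50 for euthymia, or that it would show a perfect AUC with no concordant pair. Both need the raw signed total as marker, and the 0.50 also needs equal numbers of depressed and hypomanic observations. Equal numbers are not assured, because only post-baseline visits are analysed. Since the pairs are defined through the ±8 cut-offs, an app-class marker is a plausible reading, and under it both extremes vanish. With the absolute score as marker, the euthymia AUC is likewise 1.0 under full agreement.

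The choice of marker and the handling of three states may be settled in a full protocol or analysis plan that is not shown, and the article cites a source for the method that cannot be consulted here. Their absence is not the point. What remains is the stated equation of the concordance ratio with the AUC, which fails in general under both the raw total and the app class.

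**Conclusion.** The point holds, and the sentence is wrong as written: the planned AUC does not estimate the proportion on which the trial was sized. The size of the discrepancy depends on the marker. With the raw total it can be as large as AUC 1.0 against 0% concordance in a group. With the app class it is half the difference between specificity and sensitivity. These figures assume one-versus-rest comparisons and, for the app class, concordance counted within each clinical state.

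Two wider conclusions are not supported. A reader might infer that the trial's primary result is affected, but the Outcome Measures section names changes in MADRS and YMRS as primary. A reader might also infer that N=93 is invalid, but 31 per group follows correctly from the stated proportion and precision. No data are lost either, since the same records yield the proportion.

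**What to change.** In the Statistical Analysis section:

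1. Delete the parenthesis that identifies the concordance ratio with the area under the curve.
2. Report the proportion of concordant pairs at post-baseline visits, per clinical state and overall.
3. Give a 95% CI that allows for up to four visits per patient, for example by a bootstrap that resamples patients or by GEE. An ordinary Wilson or exact interval on pooled visits would treat them as independent. Name a fallback for a state in which every pair agrees, because a bootstrap interval then has zero width. This is not remote: with one visit each and independent patients, 0.98^31 = 0.53. An exact interval on one pre-specified visit per patient would serve.
4. State how clinical scores that fit none of the three definitions are counted: MADRS above 15 together with YMRS above 8, and scores of exactly 15 on MADRS or 8 on YMRS.
5. Keep ROC only as a separate discrimination analysis, for depression versus not and (hypo)mania versus not, with the marker named.

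A weighted kappa may be added but is not needed. The cost is a change of wording and a little more analysis work. No new data or patients are required, and the sample size stays as it is.

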**Methods:**

This open-label, nonrandomized trial will enroll 93 (31 depressive, 31 euthymic, and 31 hypomanic) adults diagnosed with bipolar disorder type I/II (Diagnostic and Statistical Manual of Mental Disorders, 5th edition criteria) and owning an iPhone. Clinical evaluations will be performed by psychiatrists at the baseline and after 2 weeks, 1 month, 2 months, and 3 months during the follow-up. Rather than only accessing the daily mood symptoms, the *Toi Même* app also integrates ecological momentary assessments through 2 gamified tests to assess cognition speed (QU*i*CKBRAIN) and affective responses (PLAY*i*MOTIONS) in real-life contexts, continuously measures daily motor activities (eg, number of steps, distance) using the smartphone’s motion sensors, and performs a comprehensive weekly assessment.

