## Introduction

### Background

In clinical practice, the diagnosis and management of mood/behavioral symptoms in bipolar disorder rely on subjective information and clinician’s evaluations, thereby raising issues, including patient recall bias, decreased illness insight during acute affective episodes, and differences in clinical assessment experience [1]. In patients with bipolar disorder, mood changes are often accompanied by shifts in other behavioral patterns such as motor activity, energy, sleep, and cognitive functions [2]. In addition, many patients with bipolar disorder experience significant daily or weekly mood swings, which do not fulfill the criteria of an acute episode but are above the levels of mood/behavioral changes experienced by nonpsychiatrically ill individuals [3,4].

Mood instability in bipolar disorder increases the risk for relapse [5] and impairs daily functioning over time [6-8], indicating that the illness is still active. Evidence has shown that patients with bipolar disorder in remission who presented with emotional hyper-reactivity, which was assessed as a proxy of mood instability by using an analog self-rated scale, had significantly increased risk for cardiometabolic dysfunction and poor cognitive functioning [9,10]. A recent study using a smartphone-based mood self-monitoring in patients with bipolar disorder has shown that mood instability was associated with significantly increased perceived stress, decreased quality of life, and impaired functioning, although most of these patients were in remission during the 9-month study period [11]. These findings highlight that mood instability could provide unique additional variance in predicting bipolar illness activity. However, the longitudinal pattern of mood instability is poorly understood as it is difficult to assess validly [12,13]. Therefore, the ability to assess mood/behavior changes continuously in real time and in more ecological conditions may be an opportunity for better understanding the clinical progression of bipolar disorder and for monitoring individual treatment outcomes.

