### Objectives of This Study

In order to tackle some of these questions as well as to contribute to the evidence on digital phenotyping in bipolar disorder, we developed the *Toi Même* mHealth platform, which comprises the *Toi Même* smartphone app to self-monitor subjective and objective parameters of bipolar illness activity. The name of this project was inspired by the foreword engraved on the frontispiece of the Temple of Delphi—“Know thyself” (ie, *Connais toi toi-même,* in French). This expression was adopted by the philosopher Socrates who uttered it in his dialogues with his mentor Platon: “Know thyself as the dweller of the mind, senses, and the body” [42]. Our research protocol was carried out in real-world clinical settings with patients with bipolar disorder and we aimed to investigate the correlations between the clinically rated mood symptoms and mood/behavioral data that were automatically collected using the *Toi Même* app in patients with bipolar disorder presenting with different mood episodes. This study also aimed to assess the feasibility of this app for self-monitoring subjective and objective mood/behavior parameters in these patients.

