## Discussion

To our knowledge, this is the first study in France that has investigated correlations between clinically rated mood symptoms and mood/behavioral data automatically collected using a smartphone app specifically developed for patients with bipolar disorder through a registered clinical trial carried out in real-world bipolar disorder treatment clinics. This multidimensional digital phenotyping approach may help to improve our understanding of bipolar illness activity and potentially contribute to early detection of subtle mood/behavior changes and to objective assessment of the response to treatment and its impact on mood, cognition, emotion, and motivation in patients with bipolar disorder. In addition, the use of digital technology in bipolar disorder treatment clinics may encourage patients with bipolar disorder to monitor their health as well as reinforce the patient-clinician therapeutic alliance.

Although the *Toi Même* project is not the first to implement a smartphone-based self-monitoring tool for patients with bipolar disorder, this app was designed as an independent self-assessment tool targeting mainly the fundamental dimensions of behavior (eg, activity, energy, cognition speed, affective responses) rather than as an augmenting intervention measuring essentially mood symptoms. The *Toi Même* clinical trial has carefully followed the ethical and legal issues around providing and obtaining adequate informed content from participants, personal privacy, and safety of data collection/storage. The same clinical psychiatrist who was blinded to smartphone data collected during the study assessed the patients by using standardized rating scales. The *Toi Même* app automatically integrates behavior data collection (eg, physical activity, user’s response time) and 2 gamified modules targeting cognitive speed (QU*i*CKBRAIN) and affective response to images (PLAY*i*MOTIONS).

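### The planned comparison of the app score with MADRS and YMRS does not separate differences between patients enrolled by mood state from change within a patient, so alone it cannot support statements about tracking change

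*Protocol article*

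**What the plan says.** **Design.** The Abstract (Methods) says that the trial "will enroll 93 (31 depressive, 31 euthymic, and 31 hypomanic) adults". Sample Size repeats 31 per group and gives the presence of different mood states as the focus of the pilot.

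**Aim.** Objectives of This Study sets out to "investigate the correlations between the clinically rated mood symptoms and mood/behavioral data" in patients in different mood episodes, and to assess feasibility.

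**Change over time.** The Background motivates the app by "the ability to assess mood/behavior changes continuously in real time". Outcome Measures states that "primary outcome measures focus on changes in the severity of the depressive and manic symptoms assessed using the MADRS and YMRS". The Discussion expects that the approach may "potentially contribute to early detection of subtle mood/behavior changes and to objective assessment of the response to treatment".

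**Analysis.** In Statistical Analysis, TMP1 is the principal component that captures most variability in the eight daily items over all subjects and the whole study. It is used "to test for differences between groups in daily ratings and for comparison between this app score and the clinical rating scores". Linear mixed models with autoregressive covariance are assigned to group differences over time and are adjusted for sex, age, day of the week and elapsed time. Successive differences, the Teager-Kaiser operator, entropy and within-subject variance are planned for the daily app ratings.

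**Visits.** "Outcome measures are assessed at the baseline visit and after 2 weeks, 1 month, 2 months, and 3 months". Because app use starts at baseline, "the clinical data collected at this time point will not be included in the concordant pairs’ analysis". Four visits per patient remain.

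**The concern.** Enrolling by mood state fixes much of the between-patient spread in advance. Depressed patients should score low on the app and high on MADRS, and hypomanic patients the reverse with YMRS. An association across all patient-visits therefore arises whenever the app tells these patients apart, whether or not it moves when an individual patient's clinical score moves.

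These are two different properties. The aim of correlating app and clinical data across mood episodes can be met by the first. The text on continuous assessment, on change in MADRS and YMRS, and on early detection needs the second. The article plans one app-clinical comparison for both. Its within-subject measures do not help here, because none of them involves the clinical scores. If only a combined figure is reported, a reader cannot tell which property was shown.

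**Working it through.** **1. The plan's own figure.** For one proportion, n = 1.96² × 0.98 × 0.02 / 0.05² = 30.12, so 31 per group and 3 × 31 = 93. The stated sample size reproduces and is not in dispute.

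**2. Pooled correlation when the app tracks nothing within a patient.** The article gives no group means or SDs, so these inputs are assumptions, in units of the within-patient visit SD:
- group levels at −s, 0 and +s, equal thirds, persisting over the post-baseline visits
- patient levels varying with SD 0.5 around the group level, shared by app and clinical score
- extra patient-level noise in the app, SD 0.5
- independent visit-level deviations in each measure, SD 1.

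The variance of the group levels is B = (s² + 0 + s²)/3 = 2s²/3. Then:
- clinical variance = B + 0.25 + 1 = B + 1.25
- app variance = B + 0.25 + 0.25 + 1 = B + 1.5
- covariance = B + 0.25, of which B comes from the groups and 0.25 from the patient-level link inside groups
- pooled r = (B + 0.25) / √[(B + 1.25)(B + 1.5)]. Without the link inside groups, the numerator is B and the variances are unchanged.

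| s | B | Denominator | r with link | r without link | Group share, B/(B + 0.25) |
|---|---|---|---|---|---|
| 0 | 0 | 1.369 | 0.18 | 0 | 0% |
| 0.5 | 0.167 | 1.537 | 0.27 | 0.11 | 40% |
| 1 | 0.667 | 2.038 | 0.45 | 0.33 | 73% |
| 1.5 | 1.5 | 2.872 | 0.61 | 0.52 | 86% |

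Simulation of 93 patients with four visits each gives the same values to within about 0.01.

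**3. Does a mixed model remove this?** Not by itself. In the same simulation with the link, at s = 0.5, 1 and 1.5 (60 runs per setting):
- a random-intercept slope on the unsplit clinical score was 0.13, 0.21 and 0.30, significant in 63%, 90% and 98% of runs, although the true within-patient slope was 0
- the slope on the visit's deviation from the patient's mean was about 0, with rejections near the nominal level
- with a true within-patient slope of 0.3, the unsplit slope read 0.41 to 0.59; a rerun of 150 runs gave 0.29 to 0.30 for the deviation slope.

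At s = 0 the unsplit slope was still 0.095 (significant in 42% of 150 runs). With group in the model it stayed near 0.09 at every separation. Group adjustment thus removes the part due to enrolment but leaves the patient-level link inside groups.

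**4. Second check on scale-like scores.** Here app and clinical levels are unlinked inside groups, so any pooled association comes from the groups alone (40 replicates per scenario). With the weakest assumed separation (app means −6/0/+6, MADRS 20/8/8, YMRS 3/3/11), pooled r was −0.39 with MADRS and +0.33 with YMRS. The within-patient r was 0.02. With no separation, pooled r was about 0.01. Two wider assumed separations gave absolute r of 0.55 to 0.74. The unsplit mixed-model slope was significant in 78% to 93% of replicates in the three separated scenarios, and the deviation term in 2.5% to 7.5%. With so few replicates, these rates are rough.

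**The case against.** **The criticised model is not written down.** For the app-clinical link the article says only that the two will be compared. It names neither a pooled correlation nor a slope on the raw score, and how a covariate enters a model is often left to an analysis plan. This stands. The point is conditional: it shows what either natural choice would deliver, and asks that the split be stated. A reader might infer that the planned analysis is invalid, but the text does not fix enough to say so.

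**Telling mood states apart is a stated aim.** This stands too. A reader might infer that tracking within a patient is the app's only purpose and that the between-patient result should be demoted. Objectives of This Study and Sample Size contradict that. The Discussion's remark on early detection is hedged, and the Abstract's Conclusions call for further studies of the longitudinal pattern. Still, the Background and Outcome Measures do rest on change.

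**The group test is not purely between-patient.** Groups are compared over time with elapsed time in the model. Whether a group-by-time term is included is not stated. Such a term would describe average group trajectories, not whether a patient's app score follows that patient's clinical score.

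**The quotas do not cause all of the effect.** Correct: the first simulation gives r = 0.18 with no group separation, and only 40% of the covariance at s = 0.5 comes from the groups. If patients remit soon after baseline, the group part shrinks further.

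**Conclusion.** The point holds as a cheap improvement, not as a defect that invalidates the plan. As described, the app-clinical comparison does not distinguish differences between enrolled groups and patients from change within a patient. With no within-patient tracking at all, the pooled correlation is about 0.1 to 0.6 for group separations of 0.5 to 1.5 within-patient SDs.

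The range rests on assumed separations, on their persistence through the four post-baseline visits, and on whether app and clinical levels are linked among patients of the same group. Only its direction and rough size should be used.

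A combined association is valid evidence that the app discriminates mood states in a sample composed this way. It is not, on its own, evidence that the app follows change in a patient.

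**What to change.** In the mixed models of TMP1 on MADRS and on YMRS, using the four post-baseline visits, enter each clinical score as two terms: the patient's mean over those visits, and the visit's deviation from that mean. Report both coefficients with intervals that respect clustering by patient.

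- The between-patient coefficient speaks to discrimination of mood states. State that its size depends on the quota sampling.
- The within-patient coefficient is the basis for any statement about monitoring change.

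Do not describe the patient's mean as a usual level: it covers three months that may include an episode.

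**Cost.** The patient mean and the deviation are derived for each scale, and a few sentences are added to the analysis text; no new data are needed. The within-patient estimate will probably be smaller and less precise than a combined figure, because patients who stay stable contribute little to it.
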